# Association of Transcranial Direct Current Stimulation and Neurofeedback With Declarative Memory and Cerebral Arterial Flow in University Students: Protocol for a Double-blind Randomized Controlled Study

**DOI:** 10.2196/36294

**Published:** 2022-08-26

**Keywords:** transcranial direct current stimulation, neurofeedback stimulation, TDCS, memory, Doppler ultrasonography, arterial flow, brain stimulation, electrical stimulation, transcranial, neurofeedback, brain, neurology, cerebral, blood flow, cerebrum, declarative memory, double-blind, controlled trial, RCT, randomized controlled trial, university, college, student, postsecondary, graduate, undergraduate

## Abstract

**Background:**

The performance of a task depends on ongoing brain activity, which can be influenced by attention, excitement, or motivation. Scientific studies have confirmed that mindfulness leads to better performance, health, and well-being. However, these cognitive efficiency modulating factors are nonspecific, can be difficult to control, and are not suitable to specifically facilitate neural processing.

**Objective:**

The aim of this study is to evaluate the effects of transcranial direct current stimulation associated with neurofeedback on declarative memory and cerebral blood flow in university students.

**Methods:**

In this study, we will use transcranial direct current stimulation, a low-cost physical resource that is easy to apply, has few adverse effects, and is associated with a neurofeedback resource. This, in turn, has been shown to be a training program capable of improving working memory function.

**Results:**

Participants will be recruited between July 2022 and December 2022. This study is expected to conclude in July 2023.

**Conclusions:**

This study will provide preliminary results on the benefits of using the direct current neurostimulation and neurofeedback tools on the participants being analyzed.

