## Methods

### Study Design

This is a prospective, parallel, double-blind, randomized controlled, and 2-armed clinical trial. This study will be single center and carried out on the premises of Faculdade São Leopoldo Mandic/Campinas, São Paulo, Brazil.

After an initial evaluation carried out by a research collaborator (collaborator 1), the participant will carry out the research protocol with another collaborator (collaborator 2) according to the draw performed by this collaborator. At the end of the protocol, the participant will again undergo an evaluation that will be performed by collaborator 1. Only collaborator 2 will know if the participant performed active stimulation or placebo. Therefore, this procedure will allow blinding of the participant and collaborator 1 (evaluator) to the stimulation conditions (Figure 1).

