### Sample

The sample of 50 volunteers was calculated assuming a 40% difference in the proportion between the active TDCS and placebo groups in performance before and after the interventions. This calculation was performed using an online statistical program, considering an alpha of .05 and a power of 0.80, resulting in a sample of 25 individuals in each group (intervention and control). To approximate unexpected factors, we applied a 20% dropout rate, reaching a total sample size of 60 individuals.

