### Randomization and Blinding

Once eligibility and consent have been approved and completed, randomization will occur using the random list generated by an automated web-based randomization program. Participants will be randomly assigned into 1 of the following 2 groups:

Group A: TDCS active + neurofeedbackGroup B: placebo TDCS + neurofeedback

Participants randomized to receive placebo TDCS will have the opportunity to enroll in an open-label portion of the study upon completion of their participation in the randomized portion of the study.

This process will be carried out by a member of the research team (collaborator 3) who is not involved in the study recruitment or development process.

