As already described, neurofeedback is a brainwave training technique used to improve performance in terms of creativity, attention, and memory [24]. It has also been used as a potential cognitive and behavioral adjuvant for healthy individuals [6,25]. However, the effectiveness of neurofeedback with healthy participants received criticism from the scientific community since most studies failed to provide evidence for changes in behavioral and electrophysiological measures, mainly due to methodological deficiencies such as the lack of a sham/control group [26]. In response to this lack of reliability, Wang and Hsieh [3] researched young and older adult individuals to investigate the effectiveness of the cortical activity training protocol on attention and working memory performance. The authors observed better performance in older adults, with a significant improvement in memory among the young [3].

Although recent discoveries are addressing and answering old and new questions, the current findings provide insights into the underlying mechanisms of neurofeedback training in cognitive function. Furthermore, the results indicate that an intervention program protocol could be effective against cognitive aging and memory decline [3].

The future of neurofeedback research lies primarily in mobile recording and real-time feedback of the emotional and cognitive states of the individuals being evaluated. Due to volume conduction (the ability to measure electrical potentials at a distance from their source generators), single channels, regardless of where they are placed on the scalp, can capture a substantial fraction of all brain dynamics. Indeed, Rebolledo-Mendez et al [25] used attention levels as an input to interface systems between the brain and a computer, and found that the device provides accurate readings regarding attention since there is a positive correlation between measured and self-reported attention levels. However, setbacks observed by the authors included difficulties using the device due to the size of the head, interference with the hair, and no indicator for low batteries [25].

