To date, we have not found scientific studies using the association of the two techniques. We believe that using neurofeedback in conjunction with TDCS can potentiate the effects of training and thus provide greater effectiveness and long-term effects on the memory of individuals. In the long term, we expect that our results might further comprehensive programs for these conditions.

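### Both arms receive neurofeedback, so the trial can show only what active TDCS adds to it; the hypothesis and the planned conclusion reach further

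*Protocol article*

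**What the plan says.** **Design.** The Study Design section states: "This is a prospective, parallel, double-blind, randomized controlled, and 2-armed clinical trial". The Randomization and Blinding section gives the arms as "Group A: TDCS active + neurofeedbackGroup B: placebo TDCS + neurofeedback". Placebo participants may later enter an open-label portion, which adds no randomised control for neurofeedback.

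**Sizing.** The Sample section bases 25 per group on the TDCS contrast alone, "assuming a 40% difference in the proportion between the active TDCS and placebo groups in performance before and after the interventions", and "considering an alpha of .05 and a power of 0.80".

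**Objective and hypothesis.** The Abstract's objective is to "evaluate the effects of transcranial direct current stimulation associated with neurofeedback on declarative memory and cerebral blood flow in university students". The Introduction states the aim in similar terms, with TDCS as the thing evaluated and neurofeedback as its accompaniment. It then hypothesises a significant rise in declarative memory responses and in cerebral blood flow under the study protocol, with no comparator.

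**Conclusion and Discussion.** The Abstract's conclusion promises "preliminary results on the benefits of using the direct current neurostimulation and neurofeedback tools on the participants being analyzed". The closing Discussion gives the belief that "using neurofeedback in conjunction with TDCS can potentiate the effects of training".

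**Analysis.** The Statistical Analysis section plans t tests, or nonparametric equivalents, both inside each arm (before versus after) and between arms.

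**The concern.** Randomisation varies one component, while the promised conclusion covers two. A positive difference between Groups A and B would show that active TDCS adds something to neurofeedback. It would not show that neurofeedback works, or how the combination compares with doing nothing. A null difference would not show that the combination fails either: the Abstract's Methods paragraph describes neurofeedback as a training already shown to improve working memory, so on the authors' own account Group B is actively trained.

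The practical risk lies in the within-arm tests. As worded, the hypothesis would be met by a before-after improvement in Group A alone. If both arms improved and did not differ, that improvement could be reported as a benefit of both tools, although nothing in the trial separates it from repeating the same test.

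**Working it through.** **1. The plan's own figure and the contrast behind it.** Inputs from the Sample section: difference 40%, alpha 0.05, power 0.80, 25 per group. The base proportion and the sidedness are not given, so I assume an absolute difference and a two-sided test, and vary the base.

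n per group = [1.96·√(2·p̄·(1−p̄)) + 0.8416·√(p1(1−p1) + p2(1−p2))]² / (p2−p1)²

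For 30% vs 70%: p̄ = 0.5; 1.96 × 0.7071 = 1.386; 0.8416 × 0.6481 = 0.545; (1.386 + 0.545)² / 0.16 = 3.73 / 0.16 = 23.3, so 24.

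| Assumed proportions | n per group, no continuity correction | n per group, with correction |
|---|---|---|
| 10% vs 50% | 20 | 25 |
| 20% vs 60% | 23 | 28 |
| 30% vs 70% | 24 | 29 |
| 40% vs 80% | 23 | 28 |
| 50% vs 90% | 20 | 25 |

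The stated 25 is reproduced to within 2 for base proportions of 20% to 40% without the correction, and exactly at 10% or 50% with it. Power at 25 per group is 0.83 for 30% vs 70%. The sizing is thus consistent with an active-versus-placebo TDCS comparison, which is the contrast the design delivers.

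**2. What the two arms identify.** Write μ(T,N) for the mean outcome with TDCS active (T=1) or not (T=0) and neurofeedback given (N=1) or not (N=0). Group A estimates μ(1,1) and Group B estimates μ(0,1). No arm estimates μ(1,0) or μ(0,0).

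| Effect | Contrast | Estimable? |
|---|---|---|
| TDCS added to neurofeedback | μ(1,1) − μ(0,1) | Yes |
| Neurofeedback | μ(0,1) − μ(0,0) | No |
| Combination versus nothing | μ(1,1) − μ(0,0) | No |
| Interaction | [μ(1,1) − μ(0,1)] − [μ(1,0) − μ(0,0)] | No |

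The last three each need a cell that the trial does not contain, so a larger sample does not help.

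**3. Why within-arm tests do not fill the gap.**

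- Change in Group B = neurofeedback + (Stroop practice + time + expectation)
- Change in Group A = the same terms + the effect of TDCS given neurofeedback

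Subtracting B from A cancels the shared terms and leaves the TDCS increment. Looking at one arm alone cancels nothing.

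The documents give no practice effect, so the next figures are an illustration only. Suppose neurofeedback did nothing and practice, time and expectation shifted scores by d standard deviations of the change. A two-sided paired test with n = 25 is then significant with probability about Φ(d·√25 − 1.96):

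| Assumed d | Chance of a significant within-arm change |
|---|---|
| 0.3 | 0.32 |
| 0.5 | 0.71 |
| 0.6 | 0.85 |
| 0.8 | 0.98 |

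**4. Statements set against the estimable contrast.**

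- Abstract, conclusion: benefits of both tools. Exceeds it.
- Introduction, hypothesis: a rise under the protocol, no comparator. Exceeds it.
- Abstract objective and Introduction aim: TDCS given with neurofeedback. Compatible with it, but could also be read as the effect of the package.
- Discussion, potentiation: compatible if it means that TDCS strengthens the training; not testable if it means an interaction or a neurofeedback benefit.

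**The case against.** The strongest reply is that this is an ordinary add-on design and that the protocol mostly treats it as one. Aim, sizing and allocation all point to active versus placebo TDCS. The Abstract's conclusion is hedged as preliminary, is limited to the participants analysed, and may simply mean the two tools used together. Nothing in the randomisation, the sample size or the between-arm test is wrong.

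Much of this stands, and it rules out three stronger readings that a reader might infer.

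- *That the objective claims a benefit of neurofeedback.* It does not. TDCS is what is evaluated, and the wording fits the add-on contrast, although it is ambiguous.
- *That the Discussion asserts synergy, which would need a TDCS-alone arm.* The sentence is offered as a belief. Since the article calls neurofeedback a training, it can be read as TDCS strengthening the training, which A versus B does test.
- *That the authors contradict themselves by faulting earlier neurofeedback studies* "mainly due to methodological deficiencies such as the lack of a sham/control group". That criticism concerns studies of neurofeedback efficacy. It would count against this trial only if the trial claimed such efficacy; the stated aim concerns TDCS, which does have a sham.

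The reply does not rescue the conclusion or the hypothesis. A hedge such as preliminary speaks to precision and does not supply a missing comparator. Nor can the gap be put down to the condensed article: the arms are stated in full, and no analysis plan could recover a neurofeedback effect from them.

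**Conclusion.** The point holds as one of wording and interpretation. The design identifies one effect, active versus placebo TDCS given neurofeedback. The Abstract's conclusion and the Introduction's hypothesis go beyond it, and the planned within-arm tests could appear to support them without doing so. The objective needs clarifying, but the design does not contradict it. The potentiation statement is unsupported only if read as an interaction or as a neurofeedback benefit.

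The identification argument rests on the stated arm definitions and on no assumed number. The within-arm probabilities rest on assumed shifts and show only how easily a misleading significant change could arise. Neither the validity of the between-arm comparison nor the 25 per group is affected. What changes is what the trial may conclude.

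**What to change.** 1. State the objective and the hypothesis as a between-arm difference: active versus placebo TDCS, on the named outcomes, in students who all receive neurofeedback.
2. Limit the Abstract's conclusion to that increment.
3. In Statistical Analysis, label within-arm before-after changes as descriptive, and say that they are not evidence for neurofeedback or for the combination versus nothing.
4. In the Discussion, word the potentiation sentence as TDCS enhancing neurofeedback training, and add that the neurofeedback effect and the interaction cannot be tested here.

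The cost is a few sentences and a narrower claim. No arm or participant is added. Only if a claim about neurofeedback or the combination is wanted would more arms be needed. At the plan's own 25 per arm and before dropout, that means 3 × 25 = 75 for one added arm without active neurofeedback, or 4 × 25 = 100 for the full two-by-two layout.

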**Trial Registration:**

Brazilian Clinical Trials Registry RBR-7zs8b5; https://ensaiosclinicos.gov.br/rg/RBR-7zs8b5

**International Registered Report Identifier (IRRID):**

PRR1-10.2196/36294

## Introduction

As is well known, learning and memory involve explicit procedures (eg, declaratives) and implicit processes (eg, procedures), and improving one or both can contribute to improving learning [1]. Working memory refers to the temporary storage and manipulation of information needed for complex tasks such as language comprehension, attention, learning, and reasoning. One of the main goals of educational efforts is to develop techniques for improving learning and promoting better retention [1,2].

Today computer games are being developed not only for gamer entertainment but also in the field of health and education to improve one or more of the cognitive abilities of users. These games can improve problem-solving skills [3,4]. Brain events can be recorded in a noninvasive and flexible way through the electroencephalogram (EEG), and EEG-based applications were initially developed to help people with disabilities to communicate with machines; later they were used in video games as controllers and more recently as neurofeedback games [5]. Neurofeedback is a noninvasive, drug-free form of brain training reported to help with a variety of conditions, including pain, fatigue, depression, anxiety, sleep disturbances, and cognitive decline [6]. We can also include the implementation of a game to test the progress of trained individuals with a more flexible and interesting approach. It is a simple game application that uses visualization techniques to increase enthusiasm without being aware of being tested. As the system makes use of a participant’s direct attention to control a game, it works on a feed-forward mechanism [7]. Neurofeedback offers the possibility of endogenously manipulating brain activity as an independent variable, making it a powerful neuroscientific tool [8]. Some areas of clinical research involve comparing or combining neurofeedback with other interventions such as pharmacotherapy, behavioral therapy, and neurostimulation (eg, transcranial direct current stimulation [TDCS]).

TDCS noninvasively induces plasticity-related changes in neural circuits in vivo and is experiencing increasing use as a potential tool to modulate brain function [9]. There is growing evidence that TDCS-related outcomes are likely to be influenced by an individual’s brain state at the time of stimulation, that is, the effects show a degree of “state dependence” [10]. Fregni et al [11] demonstrated that anodic TDCS in the left dorsolateral prefrontal area leads to an increase in working memory performance, that is, increasing the accuracy of a task when compared to simulated stimulation of the same area. This study corroborates literature data showing TDCS as a tool that can significantly impact some aspects of knowledge [12].

TDCS is characterized by the administration of a single-phase electrical current of low intensity (0.5-2 mA) applied to the scalp through surface electrodes. This stimulation induces lasting changes in cortical neuronal excitability, both in animals and in humans [9]. TDCS-induced cortical modulation is dependent on the polarity of the applied current, and the effects are obtained by the movement of electrons. The poles of the electrodes used are the anode and cathode, with the anode being the positive pole and the cathode the negative pole. During the application of TDCS, the electrical current generated by the electrodes penetrates the skull, reaching the cortex [13]. Although most of the current dissipates between tissues superficial to the cortex, a sufficient amount of current reaches the cortical structures, thus modifying the membrane potential of the cells located there. It has been observed that anodic current increases cortical excitability, favoring neuronal membrane depolarization, while the cathodic current has an inhibitory effect by hyperpolarizing the neuronal membrane. TDCS has been shown to be a useful tool in the treatment of neuropsychiatric diseases and physical rehabilitation processes, being a safe and inexpensive form of noninvasive brain stimulation [10,11,14].

Some studies covering healthy individuals support the hypothesis that TDCS improves performance involving working memories, compared to simulated stimulation (placebo), and these effects can last up to 30 minutes after the end of the session. Nitsche et al [15] proposed general exclusion criteria for TDCS in healthy individuals: individuals must be free from unstable medical conditions or any disease that may increase the risk of stimulation, for example, neurological diseases such as epilepsy or acute eczema under the electrodes. Additionally, they must not have metallic implants near the electrodes. Side effects such as itchiness, a burning sensation, or a headache are common but usually mild and with no long-term impact. Thus, TDCS compares favorably with other therapeutic approaches such as antidepressants or transcranial magnetic stimulation [15].

Noninvasive neuromodulation has emerged as an alternative to replace other forms of treatment such as pharmacological treatments, which although effective, have a high rate of side or adverse effects. Among the different types, neurofeedback and TDCS have shown to be promising approaches that can modify brain wave oscillation and can be used in the development of skills for the self-regulation of brain activity [16]. However, no data were found in the literature associating these two features. The aim of this trial is to investigate the effectiveness of TDCS on the dorsolateral prefrontal cortex (DLPFC) associated with neurofeedback evaluating behavioral and physiological parameters of healthy college students. We hypothesize that there will be a significant increase in declarative memory responses and increased cerebral blood flow using the proposed protocol.

## Methods

### Study Design

This is a prospective, parallel, double-blind, randomized controlled, and 2-armed clinical trial. This study will be single center and carried out on the premises of Faculdade São Leopoldo Mandic/Campinas, São Paulo, Brazil.

After an initial evaluation carried out by a research collaborator (collaborator 1), the participant will carry out the research protocol with another collaborator (collaborator 2) according to the draw performed by this collaborator. At the end of the protocol, the participant will again undergo an evaluation that will be performed by collaborator 1. Only collaborator 2 will know if the participant performed active stimulation or placebo. Therefore, this procedure will allow blinding of the participant and collaborator 1 (evaluator) to the stimulation conditions (Figure 1).

**Figure 1 figure1:**
[figure not shown]
Flowchart of study design.

### Sample

The sample of 50 volunteers was calculated assuming a 40% difference in the proportion between the active TDCS and placebo groups in performance before and after the interventions. This calculation was performed using an online statistical program, considering an alpha of .05 and a power of 0.80, resulting in a sample of 25 individuals in each group (intervention and control). To approximate unexpected factors, we applied a 20% dropout rate, reaching a total sample size of 60 individuals.

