### Statistical Analysis

For the sociodemographic and epidemiological description of the groups, we will use the usual procedures of descriptive statistics such as calculation of frequencies and measures of central tendency and dispersion. The Shapiro-Wilk test will be performed to assess the assumption of normality of the outcome variables.

For analysis of paired and independent samples using a *t* test for comparisons within and between intervention groups or applying equivalent nonparametric tests (according to the results of the Shapiro-Wilk test) before and after the intervention, *P* values <.05 will be considered significant. Data will be organized and tabulated using SPSS (IBM Corp).

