### Outcome Variables

The guiding theme of this study is to use tools or strategies to improve learning and promote better retention. The primary expected result is a greater correctness of answers in two phases of the Stroop test (word reading and color recognition) and a decrease in test execution time.

Secondary variables are based on physiological responses of cerebral blood flow where we expect to find an increase in velocity and systolic and diastolic peaks. This hypothesis is based on functional magnetic resonance studies where the results show an increase in local blood flow after the use of TDCS.

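### The stated 80% power is for a difference in proportions that the trial does not plan to test; the primary Stroop scores and times go to t tests, whose power is not given

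*Protocol article*

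**What the plan says.** Three sections of the protocol article bear on this.

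- **Sample.** The size was "calculated assuming a 40% difference in the proportion between the active TDCS and placebo groups in performance before and after the interventions". The settings were entered as "considering an alpha of .05 and a power of 0.80", which gives 25 per arm. Then "we applied a 20% dropout rate, reaching a total sample size of 60 individuals".
- **Outcome Variables.** The accuracy part is worded as "The primary expected result is a greater correctness of answers in two phases of the Stroop test (word reading and color recognition". To this the section adds a second part, on speed: "and a decrease in test execution time". Correctness is a score for each participant and execution time is a continuous measurement. No cut-off turns either into success or failure.
- **Statistical Analysis.** The outcome variables are checked with the Shapiro-Wilk test, and the result decides between t tests for "comparisons within and between intervention groups or applying equivalent nonparametric tests". No test of proportions is listed.

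**The concern.** Power belongs to a particular endpoint, contrast and test. Here it is calculated for a difference between two proportions, while the primary outcomes are scores and times compared by their means or ranks. The power of a t test depends on the mean difference divided by the SD, and the article gives neither. The 0.80 therefore cannot be carried over to the planned comparison.

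The stake is how the result will be read. A reader will take 0.80 as the chance of detecting the effect of interest on the Stroop measures. If the true effect were moderate, the chance of missing it would be well above the 20% that the text implies.

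**Working it through.** **Inputs.** From the Sample section: 40% difference, alpha .05, power 0.80, 25 per arm, 20% dropout, 60 in total. Not given: the control proportion, whether 40% is absolute or relative, whether the test is one- or two-sided, and any Stroop mean difference or SD. I assume an absolute difference and a two-sided test, and vary the control proportion.

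**Step 1: reproduce 25 per arm.** With p̄ the mean of the two proportions,

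n = [1.960·√(2p̄(1−p̄)) + 0.842·√(p₁(1−p₁) + p₂(1−p₂))]² / (p₂−p₁)²

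and, with continuity correction,

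n′ = (n/4)·[1 + √(1 + 4/(n·|p₂−p₁|))]².

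For 10% vs 50%: n = (1.960×0.648 + 0.842×0.583)²/0.16 = (1.270 + 0.491)²/0.16 = 19.4, so 20. Then n′ = (19.4/4)×(2.231)² = 24.1, so 25.

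| Assumed proportions | Per arm, uncorrected | Per arm, continuity-corrected |
|---|---|---|
| 10% vs 50% | 20 | 25 |
| 20% vs 60% | 23 | 28 |
| 30% vs 70% | 24 | 29 |
| 40% vs 80% | 23 | 28 |
| 50% vs 90% | 20 | 25 |

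The stated 25 falls within these ranges, and 25 per arm has 82.8% power (uncorrected) for 30% vs 70%. Other readings fit less well. A one-sided uncorrected calculation needs at most 19 per arm. A relative 40% increase needs from 26 (70% vs 98%) up to 1,035 (10% vs 14%). So 25 is consistent with a two-proportion calculation for an absolute 40-point difference.

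**Step 2: compare it with the planned analysis.**

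| Element | Sample size calculation | Planned analysis |
|---|---|---|
| Outcome | a proportion | Stroop correctness and execution time |
| Effect | 40% difference | not stated |
| Variability | implied by the proportions | SD needed, not given |
| Test | two proportions | t test or nonparametric equivalent |

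**Step 3: power of the planned between-group t test.** Let d be the mean difference divided by the SD. Power comes from the noncentral t distribution with 2n−2 degrees of freedom and noncentrality d·√(n/2). For n = 25 that is 48 degrees of freedom and 3.536·d.

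| Assumed d | Power at 25 per arm |
|---|---|
| 0.3 | 18% |
| 0.4 | 28% |
| 0.5 | 41% |
| 0.6 | 55% |
| 0.7 | 68% |
| 0.8 | 79% |
| 1.0 | 93% |

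The smallest d with 80% power at 25 per arm is 0.81 (the normal approximation gives (1.960 + 0.842)×√(2/25) = 0.79). At d = 0.5, 80% power needs 64 per arm.

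**Step 4: effect of the stated dropout.** 60 × (1 − 0.20) = 48, or 24 per arm. The smallest d with 80% power is then 0.83. If all 60 were evaluable (30 per arm) it would be 0.74.

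**The case against.** The wording is loose, and proportion may not mean a responder rate. It could mean each participant's share of correct answers, or a 40% difference in the change in performance. That is fair, and it makes the authors' intention less certain. It does not rescue the calculation. A share of correct answers is still a per-person score whose power depends on an SD, a relative change in a mean needs one too, and execution time is not a proportion on any reading.

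A condensed article may also leave base rates and calculator settings to the full protocol. That stands, so the missing control proportion is not part of this point. A reader might infer that 25 per arm cannot be derived. The working shows otherwise: 10% vs 50% with continuity correction gives exactly 25.

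A reader might also infer that the trial is underpowered. The documents do not support that. They give no expected Stroop effect, so the 41% at d = 0.5 rests on an assumed effect; at d = 0.8 the same 25 per arm has 79% power. The article also promises only preliminary results, which limits how firmly a null finding would be read.

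What remains is that the basis of the calculation, the primary outcomes and the tests are all stated in the article, and they do not match. This is not detail left to an analysis plan.

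**Conclusion.** The point holds as a mismatch between the endpoint and test used for sizing and those planned for analysis. The figure of 25 per arm is credible as a two-proportion calculation, but its 0.80 power does not apply to a t test or rank test on Stroop scores and times.

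Actual power is unknown. What can be said for the planned t test, two-sided at .05, is that 80% power corresponds to a difference of 0.81 SD with 25 evaluable per arm, or 0.83 SD with 24. The article neither states nor justifies an effect of that size. If the true difference were 0.5 SD, the trial would miss it about 59% of the time (100% − 41%), not 20%.

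These figures assume a two-sided test, equal arms, normally distributed outcomes and a single primary measure. They do not carry over unchanged if the Shapiro-Wilk result sends the analysis to a nonparametric test.

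**What to change.** In the Sample section, remove the difference in proportion as the basis and keep enrolment at 60. In Outcome Variables, name which Stroop measure is primary (correctness in which phase, or time) and which between-group contrast is meant (post-intervention value or change from baseline). Without that, the SD in a power statement has no referent. Then state the power of the planned test, for example:

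> With a two-sided t test at .05, 25 evaluable participants per arm give 80% power for a between-group difference of 0.81 SD in the named measure (0.83 SD with the 24 per arm left after 20% dropout from 60).

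This reports what the chosen size can detect; it does not justify the size. If a mean difference and SD for the named measure can be supported, add them and say how they compare with 0.81 SD. Give a figure for baseline-adjusted ANCOVA only if the Statistical Analysis section is amended to plan one. Otherwise the new statement would again describe an analysis that is not planned.

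The cost is a paragraph and a clarified outcome definition, with no extra participants and no change in procedures. Enrolment has already begun according to the Results section, so the change should be made before the outcome data are analysed. The drawback for the authors is that the detectable effect becomes explicit and looks less favourable than the current text.

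### The 20% dropout allowance is added to the completers (50 x 1.2 = 60); at 20% dropout 60 enrolled leaves 48, short of the stated 50, and 60 covers only 16.7% dropout

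*Protocol article*

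**What the plan says.** The whole sample size argument stands in one paragraph of the protocol article (Methods, Sample).

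- **Target before dropout:** "The sample of 50 volunteers was calculated", split as 25 in each of the two groups.
- **Effect:** the calculation was made "assuming a 40% difference in the proportion between the active TDCS and placebo groups". No base proportions are given.
- **Error rates:** "considering an alpha of .05 and a power of 0.80". The section does not say whether the test is one- or two-sided, or which test or formula the online program used.
- **Allowance for losses:** "we applied a 20% dropout rate, reaching a total sample size of 60 individuals".

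No other section gives a different total, dropout rate or method of inflation.

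**The concern.** The allowance exists so that the calculated number of participants is still available for analysis after losses. It does that only if the percentage is taken of the people enrolled. If it is taken of the completers and added on top, the enrolled total is too small for the rate quoted. The figure of 60 looks like the second kind of calculation.

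At stake is the internal consistency of a figure that readers will rely on. The section presents 60 as enough to secure 50 evaluable participants at 20% dropout. If it is not, the trial has a smaller retention margin than it reports.

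**Working it through.** **Inputs, all from Methods, Sample:** 50 evaluable in total, 25 per arm; dropout rate d = 0.20; enrolled total 60; alpha .05; power 0.80; a 40% difference in proportion.

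**1. Reproducing the protocol's figure.** n x (1 + d) = 50 x 1.2 = 60. This matches exactly.

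**2. What a 20% dropout rate requires.** n / (1 - d) = 50 / 0.8 = 62.5, so 63. Per arm, 25 / 0.8 = 31.25, so 32, or 64 with equal arms.

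**3. What 60 delivers at 20% dropout.** 60 x 0.8 = 48, or 30 x 0.8 = 24 per arm. That is 2 short of 50, one per arm.

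**4. The dropout rate that 60 does cover.** (60 - 50) / 60 = 16.7%.

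**5. What one participant per arm means for power.** The section gives no base proportions, test or sidedness, so this step rests on assumptions: a 40-point difference, a two-sided alpha of .05, the normal approximation for two proportions, and the base rates shown.

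| Assumed proportions | No continuity correction, 25 → 24 per arm | With continuity correction, 25 → 24 per arm |
|---|---|---|
| 5% vs 45% | 93.0% → 91.9% | 86.5% → 84.7% |
| 10% vs 50% | 89.5% → 88.1% | 81.8% → 79.7% |
| 20% vs 60% | 84.5% → 82.9% | 75.8% → 73.5% |
| 30% vs 70% | 82.8% → 81.2% | 73.9% → 71.6% |

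The loss is about 1 to 2 points in every row. Without the correction, power at 24 per arm stays above 80% throughout (81.2% to 91.9%). With it, the range at 24 per arm is 71.6% to 84.7%. In the 20% and 30% rows the corrected power is below 80% already at 25 per arm, so the lost participant is not what puts it there. Only the 10% vs 50% row crosses 80% because of the lost participant.

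**6. How loosely the 25 is fixed.** Under the same assumptions, with base rates across the possible range, the requirement is 15 to 24 per arm uncorrected and 20 to 29 corrected. So 25 is attainable, but the document does not show which route led to it.

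**The case against.** The best defence is that the matter is very small. One participant per arm is lost, and the 20% is a round allowance for unforeseen events with no supporting data. The participants are healthy enrolled students attending ten sessions over two weeks, and nothing in the protocol shows that a fifth of them will leave. No comparison or endpoint depends on the point. All of this stands and limits the weight of the finding. It does not make the sentence correct.

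A second defence is that 20% was meant as an increase of 20%. The text calls it something else: "we applied a 20% dropout rate". If an increase was meant, the wording needs changing, because 60 then covers 16.7% dropout.

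A reader might go further and infer that power drops below the planned level, for instance from 80.0% to 78.3%. That figure comes from a t test with a standardised difference of about 0.81, obtained by assuming that 25 per arm gives exactly 80% power. The Statistical Analysis section does plan t tests, but the Sample section states neither that effect size nor that test; it sizes on a difference in proportions. On that basis power at 24 per arm may lie above or below 80%, as the table shows. So the documents do not support the claim that the stated power conflicts with the dropout rate. The conflict is between 60 enrolled, 20% dropout and 50 completers.

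**Conclusion.** The point holds as a minor arithmetic error in the sample size statement. As written, 60 enrolled at 20% dropout gives 48 evaluable participants, not 50, and 60 secures 50 only up to 16.7% dropout. This part needs no assumption beyond the ordinary meaning of a dropout rate as a share of those enrolled.

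The effect on power is roughly 1 to 2 percentage points under assumed base rates and a two-sided test. Whether power ends below 80% cannot be settled from the document. The error does not threaten the validity of the trial.

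**What to change.** Restate the final sentence of the Sample section in one of two ways:

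- 60 enrolled protects 50 evaluable participants against up to 16.7% dropout; or
- with 60 enrolled and 20% dropout, 48 evaluable participants (24 per arm) remain.

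Neither version should carry a revised power figure such as 78%, since the document does not give the inputs to support one.

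The cost is one sentence and a slightly less favourable retention statement. No recruitment change is needed, so the correction can still be made although the Results section reports that enrolment has begun. If the sponsor prefers to keep both 50 completers and a 20% dropout rate, the matching total is 63, or 64 with equal arms. That means three or four more participants, so it costs more than restating the sentence.
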